## Abstract

**Background:**

Childhood trauma is pervasive, with approximately 50% of adolescents experiencing at least one potentially traumatic event before adulthood. Eight percent to 33% of potentially traumatic event–exposed adolescents develop posttraumatic stress disorder (PTSD), which can cause extreme suffering and coincides with numerous comorbid illnesses and high-risk behaviors. PTSD can be effectively treated in adolescents through weekly sessions of eye movement desensitization and reprocessing or trauma-focused cognitive behavioral therapy. Despite the availability of these treatments, numerous severely traumatized adolescents do not receive available treatment options due to high treatment avoidance. In adolescents who receive care, a large group of youth does not experience a sufficient symptom decrease after regular treatment. In addition, dropout rates during prolonged treatment are substantial, varying between 10% and 30%. This underscores the need for innovative and brief trauma treatment. Pilot studies indicate that Brief Intensive Trauma Treatment (BITT) can be a safe and effective treatment for adolescents with PTSD. However, randomized controlled trials on its effectiveness are crucial and urgently needed.

**Objective:**

This is the first study to test the effectiveness of a 1-week BITT in adolescents with PTSD and comorbid symptoms and their caregivers.

**Methods:**

This multicenter, single-blinded randomized controlled trial will be conducted in 4 youth care centers in the European and Caribbean Netherlands: Levvel, Karakter, Fornhese-GGz Centraal, and Mental Health Caribbean (Bonaire). We will randomize adolescents (12-18 years old) with PTSD to a BITT (n=50) or waitlist control group (WLCG; n=50). BITT comprises 1-week (ie, 5 consecutive workdays) intensive trauma treatment, encompassing daily 90-minute manualized sessions of trauma-focused cognitive behavioral therapy and eye movement desensitization and reprocessing. The day begins and ends with psychomotor therapy. Caregivers receive daily parental counseling sessions consisting of psychoeducation and social support skill training. We will conduct measurements at similar intervals for both groups: at baseline; directly after BITT or WLCG; and at 3, 6, and 9 months’ follow-up. The WLCG will receive BITT after the 3-month follow-up assessment. We will assess all study parameters using digital or face-to-face questionnaires and semistructured interviews. We will assess the primary outcome PTSD symptoms using the Child and Adolescent Trauma Screen 2 (CATS-2) and the Clinician-Administered PTSD Scale for *DSM-5* (*Diagnostic and Statistical Manual of Mental Disorders* [Fifth Edition])-Child/Adolescent Version (CAPS-CA-5).

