### Randomization

After obtaining written informed consent from participants, an independent researcher will randomize them to either the BITT group or WLCG using computerized block-wise randomization in Castor Electronic Data Capture [38]. We will use random block sizes to avoid predictability for the researchers and we will stratify by center. The researcher completing the assessments will be blinded to the group allocation (ie, BITT vs WLC). We will explicitly instruct participants not to communicate their group allocation to the researcher.

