### Assessment Instruments

The assessments of the primary and secondary outcomes and demographic predictor variables consist of digital questionnaires and digital or face-to-face semistructured interviews administered to both the adolescents and one of their caregivers. The measurement instrument we selected for assessing the primary outcome, namely the CAPS-CA-5, is considered the golden standard for measuring PTSD. In selecting the questionnaires, we aimed to select short surveys with adequate psychometric properties. If the participant provides permission, we will audiotape the semistructured interviews. A total of 2 trained psychologists will independently code a random 15% of these sessions to measure the interrater reliability. All questionnaires will be completed in Castor Electronic Data Capture [38]. The completion time of the assessments for adolescents varies from 75 to 120 minutes per assessment moment and for the caregiver from 30 to 65 minutes per assessment moment. The overall time for therapists to complete the assessments is 20 minutes. Table 2 provides an overview of the study parameters.

**Table 2 table2:** Study parameters.

Outcomes		Assessment instrument	T0^a^	BITT^b^	T1^c^	T2^d^	T3^e^	T4^f^
Demographics		—^g^	A^h^, C^i^	—	—	—	—	—

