**Primary**								
	PTSD^j^ symptoms	CATS-2^k^	A, C	A	A, C	A, C	A, C	A, C
	Clinical diagnosis of PTSD	CAPS-CA-5^l^	A	—	A	A	A	A

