### Primary Outcomes

#### Child and Adolescent Trauma Screen

The Dutch version of the Child and Adolescent Trauma Screen 2 (CATS-2) [47,48] is a self-report and proxy-report measure for children (aged 7-18 years) and their caregivers. The questionnaire contains a list of potentially traumatic life events (16 items) and questions about PTSD symptoms (25 items; ie, re-experiencing, avoidance, emotional numbing, negative alterations in cognitions and mood, and hyperarousal). Respondents can answer each potentially traumatic life event with yes (scored as 1) or no (scored as 0). The questions about PTSD symptoms are rated on a 4-point Likert scale (range 0-3). A score of ≥2 indicates positive screening for PTSD symptoms. The highest possible total score is 60, with higher scores reflecting a higher severity of symptoms. The CATS-2 also asks informants to indicate whether the symptoms cause difficulties in daily life (yes or no). The CATS-2 has adequate psychometric properties [48].

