### Statistical Analysis

We will conduct the analyses in consultation with a statistical expert. Data analyses will include the following:

We will define the effects of BITT in terms of group differences between the BITT and WLCG. These differences will be tested according to both the intention-to-treat-principle and completers’ analyses. That is, the pre, post, and follow-up changes (BITT vs WLCG) on the continuous outcomes (ie, trauma symptoms, anxiety symptoms, depression symptoms, anger symptoms, quality of life, and self-harm) will be tested with mixed models; dichotomous outcomes (ie, suicide attempts and dropout) with generalized estimating equation (GEE).Mixed models will also be used to investigate possible moderation effects, which concern effects of (1) age, gender, SES, type of trauma, number of traumatic events, comorbidity, caregivers’ PTSD, and treatment center on PTSD; and (2) residency (ie, urban and rural) and ethnicity on BITT dropout.The qualitative interviews about the experiences of adolescents, caregivers, and therapists with regard to BITT will be verbatim transcribed and analyzed to conform to qualitative research standards.

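### The protocol article gives three conflicting accounts of the primary outcome, so it does not fix which instrument, informant or score decides the trial

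*Protocol article*

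**What the plan says.** Places in the protocol article that bear on the primary outcome:

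- **Abstract, Methods.** "We will assess the primary outcome PTSD symptoms using the Child and Adolescent Trauma Screen 2 (CATS-2) and the Clinician-Administered PTSD Scale for" DSM-5, child/adolescent version. This is one outcome (symptoms) with two unranked instruments.
- **Assessment Instruments.** "The measurement instrument we selected for assessing the primary outcome, namely the CAPS-CA-5, is considered the golden standard for measuring PTSD". This is a single instrument.
- **Table 2, Primary.** There are two rows. PTSD symptoms are measured by CATS-2, from adolescent and caregiver. CAPS-CA-5, from the adolescent only, is labelled "Clinical diagnosis of PTSD".
- **Child and Adolescent Trauma Screen.** CATS-2 "is a self-report and proxy-report measure for children (aged 7-18 years) and their caregivers". It has 25 symptom items rated 0-3, and "The highest possible total score is 60".
- **The CAPS-CA-5.** The interview yields a diagnosis and also a severity total with a maximum of 80.
- **Statistical Analysis.** Continuous outcomes, including trauma symptoms, go to mixed models, with no instrument or informant named. The binary list reads "dichotomous outcomes (ie, suicide attempts and dropout) with generalized estimating equation (GEE").
- **Power Analyses.** 66 participants (33 per arm) give at least 80% power at Cohen d=0.5, with the instrument not named. Dropout of 25% raises this to 88, and the target is 100.
- **Randomization.** The assessing researcher is blinded. Participants are not: "We will explicitly instruct participants not to communicate their group allocation to the researcher".

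**The concern.** CAPS-CA-5 is a co-measure of symptoms in one place, the only primary instrument in another and a diagnosis in a third. CATS-2 is either jointly primary or not primary at all and, where it is primary, comes in two informant versions. A favourable result on any of these could be presented as the primary result with support from some sentence in the article.

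The choice matters because the measures are not equally protected. CATS-2 is completed by adolescents who know their arm and by caregivers, who in the BITT arm attend counselling sessions themselves. Against a waitlist, such reports are the more open to expectation. The CAPS-CA-5 is scored by a blinded rater. Two of the three accounts give the two instruments equal standing.

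**Working it through.** **1. The accounts side by side**

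| Place | CATS-2 | CAPS-CA-5 |
|---|---|---|
| Abstract | primary, symptoms | primary, symptoms |
| Assessment Instruments | not named as primary | the primary instrument |
| Table 2 | primary, symptoms, two informants | primary, diagnosis |
| Statistical Analysis | not named | severity not named; diagnosis absent from the binary list |
| Power Analyses | not named | not named; the effect is continuous |

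No single reading satisfies the first three rows. The binary list is introduced as a definition (ie), so it is closed, and the diagnosis that Table 2 calls primary has no assigned analysis. The power basis is a standardised mean difference, which fits a severity score and not a diagnosis.

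**2. Error rate if any one measure can declare success**

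The article gives no alpha, sidedness or correlation between measures. I assume 5% two-sided per test and correlations between test statistics of 0.5 to 0.8.

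If independent, FWER = 1 − (1 − 0.05)^k:
- k=2: 1 − 0.95² = 9.75%
- k=3 (adolescent CATS-2, caregiver CATS-2, CAPS-CA-5): 1 − 0.95³ = 14.3%

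If correlated, P(any |Z| > 1.96) under the null, from 2,000,000 simulated multivariate normal draws:

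| Correlation | 2 measures | 3 measures |
|---|---|---|
| 0.5 | 9.1% | 12.5% |
| 0.6 | 8.8% | 11.7% |
| 0.7 | 8.4% | 10.9% |
| 0.8 | 7.8% | 9.8% |

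**3. Price of the alternatives to a single primary**

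Here I take the article's 80% at 66 evaluable as given. Whether 66 can be reproduced is a separate matter. The dropout step does reproduce: 66/0.75 = 88.

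- *Bonferroni, 2.5% each.* Power = Φ(1.960 + 0.842 − 2.241) = Φ(0.560) = 71.2%. To restore 80%: 66 × [(2.241 + 0.842)/(1.960 + 0.842)]² = 66 × 1.211 = 79.9, so 80 evaluable, and 80/0.75 = 107 randomised against a target of 100. At 75 evaluable (100 less 25%), power is 77.2%, compared with 84.8% at 5%.
- *Both must succeed, 5% each.* Alpha is not inflated. With 80% for each test, joint power lies between 0.80 × 0.80 = 64% (independent) and 80% (perfectly correlated).
- *One primary, or a fixed sequence.* The 5% level is kept and the sample size is unchanged.

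**4. CATS-2 score**

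25 items × 3 = 75, not 60. A maximum of 60 corresponds to 60/3 = 20 summed items. The article does not say which.

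**The case against.** The strongest reply is that this is a journal article. A multiplicity rule, a testing order and the exact form of each model are commonly left to a full protocol or analysis plan, neither of which is shown. That stands, and the absence of an alpha rule is not the point here. It does not answer the conflict between the abstract, the Assessment Instruments section and Table 2, which an unseen document leaves in print.

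Several stronger readings are tempting but not supported:

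- *CAPS-CA-5 has no planned analysis.* This holds only for the diagnosis. The 0-80 severity total can fall under the mixed model for trauma symptoms, and the abstract treats the instrument as a symptom measure.
- *The type I error is inflated.* This is so only if any single measure may declare success. The article states no decision rule.
- *Two instruments at two visits push the error to 13-16%.* This needs separate tests at each visit. The article describes changes over time in mixed models and does not state such tests.
- *Eligible subthreshold cases would be counted as free of PTSD.* No loss-of-diagnosis endpoint is defined, so this is a caution for writing one, not an error in the plan.

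The blinding contrast also has a limit. The CAPS-CA-5 rater is blinded, but the adolescent who answers is not, so the interview reduces rater bias without removing expectation from the answers. The trial openly calls itself single-blinded. Finally, the 60/75 discrepancy is a separate reporting error and does not bear on which instrument is primary.

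**Conclusion.** The concern holds as an internal contradiction. The article does not settle whether CATS-2, CAPS-CA-5 or both are primary, which CATS-2 informant counts, or whether CAPS-CA-5 enters as severity or as diagnosis. The diagnosis shown as primary in Table 2 has no analysis.

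The size is conditional. Under an any-one-succeeds rule at an assumed two-sided 5%, the family-wise error is about 8-9% for two measures and about 10-12.5% for three at correlations of 0.5-0.8, with 9.75% and 14.3% as the independent limits. Under a both-must-succeed rule there is no inflation and the cost is joint power.

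This should be settled before unblinding, because afterwards the choice of deciding result could no longer be shown to be independent of the data.

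**What to change.** Reconcile the abstract, Assessment Instruments, Table 2 and Statistical Analysis on one hierarchy, dated before unblinding:

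1. **Primary:** CAPS-CA-5 total severity (0-80) by the blinded rater, BITT versus waitlist at T2, tested in the planned mixed model. This follows the Assessment Instruments section and fits the continuous power basis. T2 is the last assessment before the waitlist receives BITT. CAPS-CA-5 asks about the past month, so at T1, directly after a one-week treatment, much of its recall window would precede the end of treatment.
2. **First key secondary:** adolescent CATS-2, tested only if the primary is significant. Caregiver CATS-2 is supportive.
3. **Secondary binary:** CAPS-CA-5 diagnosis, added to the list of dichotomous outcomes with a stated analysis. If loss of diagnosis is analysed, restrict it to participants with full PTSD at baseline.
4. **Separately:** correct the CATS-2 scoring, stating which 20 items are summed if 60 is the maximum, or giving 75 if all 25 are.

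The cost is wording. Conduct and sample size do not change, and the 5% level is kept. The downside is that CATS-2 can no longer carry the trial alone.

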**Results:**

As of September 2022, we enrolled 104 participants. Data will be collected until December 2025. Results are expected to be published in the summer of 2026.

**Conclusions:**

This first, innovative study on BITT’s effectiveness may enhance treatment outcomes for PTSD by preventing dropout, reducing avoidance, shortening therapy duration, and empowering therapists by working together intensively. This research will provide valuable insights across cultures for treating severely traumatized adolescents who do not benefit sufficiently from regular treatment.

**Trial Registration:**

ClinicalTrials.gov NCT06143982, http://clinicaltrials.gov/ct2/show/NCT06143982

**International Registered Report Identifier (IRRID):**

DERR1-10.2196/66115

## Introduction

Childhood trauma is pervasive, with around 50% of adolescents experiencing at least one potentially traumatic event (PTE) before adulthood [1-3]. Posttraumatic stress disorder (PTSD) is the most common disorder that can develop after experiencing PTE and occurs in around 16% of PTE-exposed adolescents, with a range of 8%-33%. Importantly, the variability within this range is influenced by the type of trauma and gender. In particular, PTSD is less prevalent in boys exposed to noninterpersonal trauma, while girls exposed to interpersonal trauma are at a greater risk of developing PTSD [4]. PTSD manifests through symptoms such as re-experiencing (ie, flashbacks, nightmares, dissociation, repetitive distressing images or sensations, and physical sensations such as pain, sweating, nausea, or trembling), avoidance and emotional numbing, negative alterations in cognitions and mood, and hyperarousal (ie, irritability, angry outbursts, sleep disturbances, and difficulty concentrating) [5].

Furthermore, PTSD significantly affects an individual’s quality of life [6,7]. Adolescents with PTSD have been found to show high rates of psychopathology at the age of 18 years, including 48.8% engaging in self-harm, 20.1% attempting suicide, 54.7% diagnosed with major depressive disorder, 23.8% with generalized anxiety disorder, and 27% with conduct disorder [8]. In addition, subclinical PTSD (sPTSD) in adolescents is often neglected. However, adolescents with sPTSD can experience similar distress as adolescents with full-blown PTSD [9]. These findings emphasize the critical importance of early treatment for both clinical and sPTSD.

The internationally recommended treatment guidelines for PTSD are weekly sessions of eye movement desensitization and reprocessing (EMDR) or trauma-focused cognitive behavior therapy (TF-CBT) [10-13]. However, 30% of individuals do not benefit enough from evidence-based PTSD treatments. This might be explained by PTSD symptom severity and high rates of psychiatric comorbidity within this group of patients. Notably, greater symptom severity and high rates of comorbidity are associated with reduced treatment success [14]. In addition, dropout rates during prolonged treatment are substantial, varying between 10% and 30% [15-18]. The duration of therapy and treatment avoidance potentially cause these dropout rates. Current treatment strategies are prolonged (at least 3-4 months) and, therefore, subject to engagement and compliance barriers. For example, adolescents can be reluctant to engage in therapy due to fear of re-experiencing their trauma over a long period of time [19]. Due to frequent appointments over a longer period, adolescents miss school time and the opportunities to engage in hobbies, social activities, and peer contact, hampering healthy development and resulting in therapy disengagement. Notably, a greater number of therapy sessions is found to be an important predictor of dropout in adolescents with trauma [20]. These findings underline that innovative trauma treatments are crucial and that treatments in a novel, brief, and intensive format are urgent.

Brief Intensive Trauma Treatments (BITT) entail multiple trauma-focused sessions, often integrating various treatment modalities simultaneously. Recent studies have indicated that BITT for adults can serve as a safe and effective strategy for reducing PTSD [21-24]. These studies have yielded promising outcomes in adults, characterized by notably low dropout rates and minimal adverse events. Unfortunately, evidence of the effectiveness of brief trauma treatments in children and adolescents is limited. To date, only 9 studies have shown promising results [25-33]. However, 8 of the 9 studies were conducted without control groups and all studies had relatively small sample sizes (ie, N=10, N=27, N=22, N=15, N=15, N=33, N=44, N=27, and N=36). Hence, from the perspective of clinical relevance and optimizing treatment and healthy development of children with trauma, randomized controlled trials (RCTs) investigating the effectiveness of BITT in adolescents are urgently needed. This was the rationale for the present innovative multicenter RCT. This RCT follows up on a pilot study (N=22) of the same BITT program, which previously demonstrated promising results, including a reduction in PTSD symptoms up to 3 months post treatment [34].

## Methods

### Aims

#### Primary Objective

The primary objective of this RCT is to assess the effectiveness of a BITT compared to a waitlist control group (WLCG) in reducing symptoms of PTSD among adolescents aged 12-18 years.

#### Secondary Objectives

The secondary objectives of the study are to investigate whether BITT for adolescents with PTSD:

in comparison to a WLCG, demonstrates effectiveness in reducing comorbid psychiatric symptoms (ie, anxiety, depression, and anger) and improving the quality of life;is safe (ie, does not increase suicide attempts or self-harm)reduces dropout rates;is affected by moderators (ie, age, gender, socioeconomic status [SES], type of trauma, number of traumatic events, comorbidity, caregivers PTSD, and treatment center) in its effect on PTSD symptoms and BITT dropout (moderators: residency [ie, urban and rural area] and ethnicity).

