**Figure 1 figure1:**
[figure not shown]
Flowchart of the randomized controlled trial design. BITT: Brief Intensive Trauma Treatment.

The treatment phase of BITT lasts only 1 week (ie, 5 consecutive workdays). The WLCG will not receive psychological care (ie, EMDR and TF-CBT) during this week. After this week, participants from the BITT group will follow regular follow-up care, which usually consists of EMDR and TF-CBT. Apart from BITT, the WLCG can receive any treatment including EMDR and TF-CBT, during this period. We will monitor and register all provided care in the research database (inclusion and exclusion criteria listed in Textbox 1).

Inclusion and exclusion criteria.Inclusion criteriaParticipants must meet all of the following criteria:12-18 years of age;A history of psychological trauma (as measured by the Life Events Checklist of the Clinician-Administered Posttraumatic Stress Disorder Scale for Children and Adolescents in the *DSM-5 [Diagnostic and Statistical Manual of Mental Disorders* (Fifth Edition)]) [35,36];At least subthreshold posttraumatic stress disorder criteria, conform to the Clinician-Administered PTSD Scale for Children and Adolescents *DSM-5*, that is:fully meets criteria A, F, and G, and at least one symptom of criteria B, C, D, and E;fully meets criteria A, F, G, and at least one of the B, C, D, or E symptom clusters;The adolescent must provide written informed consent. For adolescents aged 12-15 years, all legal guardians must also provide consent.Exclusion criteriaAdolescents who meet any of the following criteria will be excluded from participation in this study:inability to speak and write Dutch;estimated or determined intellectual disability (IQ <70);having ongoing trauma by a parent who is part of the adolescent’s current primary care system.

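### The BITT versus waitlist comparison cannot show that BITT reduces treatment dropout, because before T2 the waitlist has no assigned treatment to drop out of

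*Protocol article*

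**What the plan says.** All references are to the protocol article.

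- **Secondary Objectives.** One aim is that BITT "reduces dropout rates". No comparator is named in that item; the comparison with the waitlist is written only into the first item of the list.
- **Statistical Analysis, definition of effects.** "We will define the effects of BITT in terms of group differences between the BITT and WLCG". Dropout is among the outcomes tested this way: "dichotomous outcomes (ie, suicide attempts and dropout) with generalized estimating equation (GEE").
- **Statistical Analysis, moderators.** "Mixed models will also be used to investigate possible moderation effects", and these include effects of "residency (ie, urban and rural) and ethnicity on BITT dropout". Earlier in the same section, mixed models are given to the continuous outcomes, a list that ends "quality of life, and self-harm) will be tested with mixed models".
- **Study Design, text under Figure 1.** "The WLCG will not receive psychological care (ie, EMDR and TF-CBT) during this week". After the week, controls may take any care other than BITT, including EMDR and TF-CBT, and the BITT arm moves to regular follow-up care. All care is registered. Controls receive BITT after the 3-month assessment.
- **Introduction.** The reason for interest in dropout is the 10% to 30% seen in prolonged treatment.
- **Abstract, Conclusions** (repeated in substance in the closing Conclusions). The study "may enhance treatment outcomes for PTSD by preventing dropout, reducing avoidance, shortening therapy duration".

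**The concern.** To say that a treatment reduces dropout, one needs a second treatment from which people could also drop out. The one comparator the analysis section supplies is a waitlist. During the BITT week a control participant can leave the study but has no therapy to abandon. From then until T2, any therapy that a control takes up, and may leave, is optional and varies from person to person.

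The comparison that motivates the aim, BITT against weekly trauma therapy over several months, is not randomised here. A BITT versus waitlist p-value for dropout could nevertheless be read as evidence for it, and the conclusions already name preventing dropout as a way in which BITT may help.

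A related problem is that BITT dropout can occur only in people who start BITT. Residency and ethnicity can predict it, but they cannot moderate a between-arm effect on it.

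**Working it through.** **1. The plan's own dropout figure.** Power Analyses inflates 66 participants for 25% dropout: 66 / (1 − 0.25) = 88, as stated. The rate is taken from trauma-focused therapies but is applied to the whole sample, waitlist included. The article thus uses one word for leaving therapy and for loss to the analysis.

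**2. What each arm can drop out of, by period.**

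| Period | BITT arm | Waitlist arm | What a between-arm difference can mean |
|---|---|---|---|
| BITT week, to T1 | BITT, 5 workdays | No EMDR or TF-CBT, no BITT | Study attrition only; BITT non-completion has no counterpart |
| T1 to T2 | Regular follow-up care | Any care except BITT, optional | Study attrition, or disengagement from unassigned care |
| After T2 | Follow-up | BITT | Both arms have had the same treatment offered |

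In no row is BITT set against an assigned course of weekly therapy.

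**3. What can be estimated.** BITT non-completion is a single proportion. The exact (Clopper-Pearson) 95% limits for x events in n are the 0.025 quantile of Beta(x, n − x + 1) and the 0.975 quantile of Beta(x + 1, n − x). The rates are assumptions, taken from the ends of the article's 10% to 30% range.

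| Assumed rate | 50 immediate starters | 100 starters, both arms |
|---|---|---|
| 10% | 5/50: 3.3% to 21.8% | 10/100: 4.9% to 17.6% |
| 30% | 15/50: 17.9% to 44.6% | 30/100: 21.2% to 40.0% |

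The figure of 100 assumes that every control goes on to start BITT. If, for illustration, 25% of controls were lost first, 50 × 0.75 = 37.5 would remain, or about 87 starters in all.

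**4. Events available for the predictor analysis.** 50 × 0.10 to 50 × 0.30 gives 5 to 15 events; 100 starters give 10 to 30. With an even split on a binary predictor and two-sided 5% alpha (assumed, as the article states none), power to separate 35% from 15% is 37% with 25 per group and 64% with 50 per group.

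**5. Illustration only.** Suppose both arms did have a treatment to leave. With 50 per arm and the same alpha, using z = [|p1 − p2| − 1.96 √(2p̄(1 − p̄)/n)] / √([p1(1 − p1) + p2(1 − p2)]/n), power is 51% for 25% versus 10%, 71% for 30% versus 10% and 81% for 25% versus 5%. The main difficulty is what the comparison means; precision comes second.

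**The case against.** Several points on the other side are sound.

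- **Controls are not without care throughout.** After the BITT week they may take EMDR, TF-CBT or other care, and it is registered. A reader might infer that the waitlist has no treatment dropout at all, or that no randomised dropout comparison exists. The documents do not support either. Study attrition by arm at T1 and T2 is a valid randomised comparison. Disengagement from care can also be compared by arm, although it is hard to interpret because uptake is optional.
- **The models are not wrong as such.** A reader might infer that GEE and mixed models cannot handle a one-off yes/no event. GEE with one binary value per person is logistic regression with robust standard errors, and the term mixed models does not exclude a logistic mixed model, for example with a centre effect. What stands is inconsistent wording: dropout is assigned to GEE, and its moderators then to the model class given to continuous outcomes.
- **Definitions may sit elsewhere.** The aim names no comparator, and an operational definition of dropout may be in the full protocol. This helps only in part. The article itself applies the BITT versus waitlist definition to dropout and names no other comparator.
- **Moderator versus predictor is partly a label.** The phrase used in the analysis section already describes an effect on BITT dropout, so relabelling may change no computation. It does prevent the result being read as a difference in treatment effect.
- **The conclusion is hedged.** It says what BITT may do and reports no result, so misuse of a p-value is a risk and not a certainty.

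**Conclusion.** The concern holds for the aim and its comparator. The planned between-arm test of dropout can show differences in study attrition, possibly mixed with disengagement from optional care. It cannot show that BITT lowers treatment dropout relative to prolonged weekly therapy. This rests on the article's own description of the waitlist and needs no numerical assumption.

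What the trial can deliver is a descriptive non-completion proportion. At an assumed 10%, the upper 95% limit is 21.8% with 50 starters and 17.6% with 100. Setting such an estimate beside the cited 10% to 30% would be a non-randomised comparison. With about 5 to 15 events in 50, or 10 to 30 in 100 if all start, the residency and ethnicity analysis is exploratory.

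On the models, the finding is limited to inconsistent wording and the moderator label. The point touches one secondary aim and its wording in the conclusions; the primary analysis is unaffected.

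**What to change.** 1. Restate the aim as estimating the BITT non-completion proportion, with an exact 95% confidence interval, among all who start BITT. Show it for immediate starters, for delayed starters and pooled. Define non-completion separately from leaving the study.
2. Report study attrition by arm at T1 and T2 as a separate randomised comparison, and state that it is not to be interpreted as reduced treatment dropout.
3. Call residency and ethnicity exploratory predictors of BITT non-completion and name one binary-outcome (logistic) model for them. A penalised version is an option if events are few, but is a matter of preference. Align the two sentences in Statistical Analysis accordingly.
4. In both conclusions, mark preventing dropout as not tested by the randomised comparison.

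The cost is wording and one descriptive estimate; no added participants or assessments are called for. The downside is that a comparative secondary claim becomes descriptive.
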